**Fig. 2 Fig2:**
[figure not shown]
Schedule of enrolment, interventions, and assessments. BMI, body mass index, NRI, Nutritional Risk Index; CCI, Charlson Comorbidity Index; NIV, noninvasive ventilation; CPAP, continuous positive airway pressure

### Sample size {14}

Given a type I error of 0.05, a power of 0.8, an expected proportion of patients who develop pressure sores in the control group of 23% [39], and an expected dropout rate of 5%, 239 subjects per group are estimated to identify a 10% absolute difference in the proportion of patients developing pressure sores between intervention and control groups measured at 36 h from randomization.

### Recruitment {15}

A survey was administered during the planning phase of the protocol to identify possible recruiting centers and estimate the number of patients that each center could possibly enroll in the study period. Thereafter, the list of the participating centers was redacted and proposed. In case a problem of low recruitment is encountered, any center with a consistently low recruitment rate will be contacted to address site-specific issues. If necessary, new investigators and sites will be added to overcome low recruitment rates.

## Assignment of interventions: allocation

### Sequence generation {16a}

Computer-based random sequences will be generated by the statistician in charge of the analyses. A total of 240 random extractions from a Bernoulli distribution with a probability equal to 0.5 will be performed to assign patients 1:1 to the interface rotation (treatment) or standard of care (control) group. Moreover, following the same procedure, patients in the interface rotation group will be assigned to start their treatment wearing an oronasal mask or full face/hybrid masks. The randomization list will be uploaded into the research electronic data capture (REDCap) system that will provide the assigned arm of the patients. Investigators will have no access to the randomization list.

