## Methods: participants, interventions, and outcomes

### Study setting {9}

Data will be collected from ICUs, intermediate respiratory care units, respiratory medicine, or internal medicine services in 23 centers in Italy.

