### Intervention description {11a}

In the control group, mask will be chosen among the three types of masks available: oronasal, total face, or hybrid mask, according to the standard of care of the participating centers. Patients wearing oronasal masks will receive protective dressing on their nasal bridges before starting NIV. Interface will be changed in case of discomfort, referred by the patient as unbearable, or in the presence of a pressure sore.

In the intervention group, the mask initially applied to the patient will be randomly chosen between the two most used masks in that center among those available (i.e., oronasal, total face, or hybrid mask). Thereafter, NIV mask will be changed every 6 h, alternating the two different interfaces. Patients wearing oronasal masks will receive a protective dressing on the nasal bridge before starting NIV. In case of discomfort, referred by the patient as unbearable related to one of the two interfaces, NIV will be continued with the other mask.

In both arms, the treatment will be continued until patients require NIV according to the assigned protocol.

Prior to patient recruitment, the candidate assessors (doctors and nurses) will be trained to recognize and stage pressure sores through a specific standardized education module. At the end of this course, the trainees will be asked to take a final test where they have to correctly stage 10 pressure sores. Only those trainees able to identify and stage all 10 sores will be qualified as assessors. To minimize detection bias, assessors will not participate in patient care and will be blinded to treatment allocation.

The skin underneath the mask and occipital region will be inspected every 12 h for possible damage by the assessors. If a pressure sore is detected, the physician in charge of the patient will be promptly informed, and a note will be written on the nursing record. Pressure sores will be staged according to the classification of the National Pressure Ulcer Advisory Panel, European Pressure Ulcer Advisory Panel, and Pan Pacific Pressure Injury Alliance [36] (Table 1).

**Table 1 Tab1:** Pressure sores classification according to the classification of the National Pressure Ulcer Advisory Panel, European Pressure Ulcer Advisory Panel, and Pan Pacific Pressure Injury Alliance

Stage I	A reddened, painful area on the skin that does not turn white when pressed. This is a sign that a pressure ulcer may be forming. The skin may be warm, cool, firm, or soft.

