The analyses will be also performed according to the modified intention-to-treat approach (mITT) excluding subjects with a NIV duration shorter than 12 h to ensure patients in the rotational group performed at least one rotation of the interface.

Regarding the economic evaluation, the incremental cost-effectiveness ratio (ICER) will be calculated considering two outcomes: (i) the proportion of pressure sores and (ii) the patient comfort. ICER, which is the ratio between the difference of each outcome in the two groups (i.e., difference in the proportion of pressure sores or comfort score) and the difference in the average cost for each treatment will allow to evaluate the incremental costs needed to reduce of 1 point the outcomes thanks to interface rotation. The confidence intervals of the ICER will be calculated using the non-parametric bootstrap method. Specifically, the 2.5^th^ and 9.75^th^ percentiles of the bootstrap distribution of ICER will be considered as the lower and higher limits of the confidence interval. The cost-effectiveness acceptability curve will also be drawn to evaluate the probability of the intervention to be cost-effective, considering different thresholds.

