### Methods for additional analyses (e.g., subgroup analyses) {20b}

When possible (i.e., enough patients are available), the analyses will be performed stratified by center.

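### Allocation is unrestricted and unstratified across 23 centres although the centre determines the masks in both arms: valid and unbiased, but a small, avoidable loss of precision

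*Protocol article*

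**What the plan says.** **Allocation.** Under Sequence generation {16a}, "random extractions from a Bernoulli distribution with a probability equal to 0.5 will be performed to assign patients 1:1". The number of draws is 240, and the result is a single list loaded into REDCap. No centre, block or stratum is mentioned. That the scheme is unstratified is read from this procedure; the article does not use the word.

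**Centres.** Study setting {9} lists intensive care, intermediate respiratory care, respiratory medicine and "internal medicine services in 23 centers in Italy".

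**What the centre decides.** Under Intervention description {11a}, the control mask is selected "according to the standard of care of the participating centers". In the rotation arm the first mask is "randomly chosen between the two most used masks in that center", and the patient then alternates within that pair. The masks in both arms therefore depend on the site.

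**Where centre enters the analysis.** The mixed logistic model in Statistical methods {20a} has a random intercept for centre. Under Methods for additional analyses {20b}, where numbers permit, "the analyses will be performed stratified by center". The raw risks in {20a} are stated without centre. So is the cost-effectiveness ratio, which compares sore proportion, comfort and "the difference in the average cost for each treatment".

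**The concern.** The plan treats centre as a factor at analysis but does nothing about it at allocation. Independent draws give no balance within a centre, even if the list were later divided by site or happened to total exactly 239 per arm. Where one arm is over-represented in a centre, that centre contributes less to the treatment comparison. Contrasts that ignore centre pick up part of any difference between centres as noise. Small centres may contribute little to a centre-stratified analysis. At stake is precision at the 36 h comparison, in a design with almost no power in reserve after dropout.

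**Working it through.** **Inputs from the protocol article.** Sample size {14} sets alpha at 0.05 and power at 80%. For the comparator it takes "an expected proportion of patients who develop pressure sores in the control group of 23" per cent. The difference sought is 10 points (so 23% against 13%), dropout is 5%, and the result is 239 per group (478 in total). Study setting {9}: 23 centres.

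**Assumptions.** The article gives no intraclass correlation (ICC) between centres; 0.01 to 0.20 is assumed. It gives no centre sizes; equal sizes (20 or 21) or skewed sizes (4 to 58) are assumed. The test is taken as two-sided.

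**1. The plan's own figure.** With unpooled variance, n = (1.96 + 0.8416)² × (0.23×0.77 + 0.13×0.87) / 0.10² = 227.8 per group. Taking 227, 227/0.95 = 238.9, so 239: reproduced. (228/0.95 = 240; the pooled formula gives 231, then 244.) By the pooled formula, power is 81.4% at 478 patients and 79.4% at 454 after dropout.

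**2. Splits within a centre.** 478/23 = 20.8 patients per centre. For 21 coin-flip allocations the arm difference has SD √21 = 4.6. P(14:7 or worse) = 2 × P(X ≤ 7) = 2 × 198,440/2²¹ = 18.9%, or about 0.189 × 23 = 4.3 centres if all had 21 patients. About 41% of centres (equal sizes) to 48% (skewed sizes) would be split 60:40 or worse.

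**3. Upper bound on the loss.** In a centre-stratified or fixed-centre analysis, a centre of size m with n₁ and n₂ patients per arm contributes information n₁n₂/m. If balanced this is m/4. Under coin flips E[n₁n₂] = m(m−1)/4, so the expectation is (m−1)/4. The loss is exactly one patient per centre on average: 23 of 478, or 4.8%. Power goes from 81.4% to 79.5% at 478, or from 79.4% to 77.3% at 454.

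**4. Loss under the planned random intercept.** This model recovers some between-centre information, so less is lost. Generalised least squares information, simulated over 5,000 allocations with equal centres, gives:

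| ICC | Effective N | Patients lost | Per centre | Power |
|---|---|---|---|---|
| none lost | 478 | 0 | 0 | 81.4% |
| 0.01 | 473.2 | 4.8 | 0.21 | 81.0% |
| 0.05 | 465.5 | 12.5 | 0.54 | 80.4% |
| 0.10 | 461.7 | 16.3 | 0.71 | 80.1% |
| 0.20 | 458.5 | 19.5 | 0.85 | 79.8% |

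The cost is 0.4 to 1.6 power points. Skewed centres give a similar range, about 0.2 to 0.8 patient per centre. The power column applies the two-proportion formula to the effective N, so it approximates the logistic model.

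**5. What restriction would recover.** With blocks of 4 per centre the fixed-centre loss falls from 23 patients to about 0.9 to 1.4 in total; with blocks of 6, to about 1.9 to 2.3.

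**6. Direct simulation.** Six settings of 1,500 runs were used, with an assumed between-centre SD of log-odds of 0.5 to 1.1. Mean power, coin flips against centre blocks, was 81.8% against 82.7% (mixed logistic model), 80.7% against 82.2% (Cochran–Mantel–Haenszel) and 79.3% against 80.2% (crude). The SD of the crude risk difference fell by 0.5 to 4%. The Monte Carlo standard error of each power difference is about √(2×0.82×0.18/9000) = 0.6 points, so the 0.9-point gains are not sharply separated from zero.

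**7. Price in predictability.** Someone who always guesses the arm behind in a complete block of size 2b expects b + 2^(2b−1)/C(2b,b) − ½ correct guesses. That is 2.83 of 4 (71%), 4.10 of 6 (68%) and 6.53 of 10 (65%), against 50% under coin flips. The guesser is taken to know where blocks start; random, undisclosed sizes make that harder.

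**The case against.** The strongest reply is that this is a preference. Simple randomisation is valid, and it is the least predictable scheme, which counts for something when care providers are unblinded. Centre is in the model, the centre-stratified analyses are conditional on numbers, the raw risks are descriptive, and bootstrap intervals for the cost-effectiveness ratio express sampling noise. All of that stands. It keeps the point to an efficiency improvement; it does not remove it.

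Three stronger readings are tempting and are not supported:

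- **That one patient's information per centre is lost in the main analysis.** That figure belongs to a centre-stratified or fixed-centre analysis. For the planned random intercept it is an upper bound.
- **That each centre also sets its own skin care.** Relevant concomitant care {11d} has every site adopt a skincare bundle and sets common rules for mask size and strap tension. Intervention description {11a} requires nasal-bridge dressing with oronasal masks in both arms, and {11c} selects centres with similar rotation practice. What demonstrably varies by centre is the mask.
- **That the 2 to 31% incidence range in the Background is a spread between these centres.** It comes from published reports and is attributed there to several other factors as well, including treatment length and nutritional status.

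The reply is also right that changing the scheme is not free: approval is needed at each centre, and allocation becomes somewhat more predictable.

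**Conclusion.** The point holds as a cheap improvement, not as an error. The described scheme leaves within-centre balance to chance in a trial where the centre determines the masks in both arms and is accounted for at analysis. A reader might infer that the comparison is biased, or that every centre will be unbalanced. Neither follows: the imbalance is a matter of chance, and it costs precision only. The expected loss is about 5 to 20 of 478 patients under the planned model (0.4 to 1.6 power points) and at most 23 (about 2 points) in a centre-stratified analysis, plus slightly more noise in the raw risks and economic contrasts. These sizes rest on the assumed ICC and centre sizes, and on the stated 23 centres and 478 patients. With little between-centre variation the loss under the planned model is close to nil.

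**What to change.** As written, 240 draws cannot allocate 478 patients, so the list has to be regenerated in any case. When that is done:

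- Generate one list per centre in REDCap with restricted randomisation: permuted blocks of randomly varying, undisclosed and preferably larger sizes, or another scheme that limits imbalance within centre.
- Keep the allocations already made; the coordinating centre moves to its new list from that point.
- Keep centre in the model.

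**Cost.** The work is a new list, an upload and a protocol amendment. Under the amendments section {25}, the amendment needs approval by the review board of each participating centre. According to Trial status, only the coordinating centre had begun recruiting at publication and the others were still in ethics evaluation, which limits the disruption. The coordinating centre would have a mixed scheme. Some predictability is introduced in an open-label trial; random, undisclosed block sizes reduce it but do not remove it.

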### Concealment mechanism {16b}

To ensure allocation concealment, the randomization list will be uploaded directly into REDCap. Allocation will take place after the patient is recruited to the trial.

## Assignment of interventions: blinding

### Who will be blinded {17a}

Due to the nature of the intervention tested, trial participants and care providers will not be blinded after being assigned to an intervention. However, assessors and data analysts will not participate in the care of the patient and will be blinded to patient group assignment.

### Procedure for unblinding if needed {17b}

Unblinding procedure is not required.

## Data collection and management

### Plans for assessment and collection of outcomes {18a}

A REDCap database will be set up to collect the information needed for the study. The database will consist of ten sheets. The first one will contain the baseline demographic and clinical characteristics of the patients. Eight sheets will store information on primary and secondary outcomes at each time point. The last one will enlist information on patient discharge and the overall treatment. More specifically, the following variables will be recorded:*Baseline characteristics*: age, sex, hospitalization date, nutritional status, body mass index, Braden scale, frailty index, sensorium (Kelly score), Charlson index, chronic steroids therapy, domiciliary NIV or CPAP, NIV treatment goal.*Outcome assessment:* presence and number of pressure sores, location, comfort score (numerical rating scale from 1 to 5), stage for each lesion, fever, humidification, vasoactive medication, NIV interruption, daily NIV duration, hygiene protocol application, eye irritation, interface change, time interface change, NIV ventilator, circuit type, expiratory positive airway pressure, inspiratory positive airway pressure, leaks, medical treatment for the pressure lesions and eventual skin specialist consult.*Discharge:* discharge date, length of hospital stay, discharge status.

### Plans to promote participant retention and complete follow-up {18b}

Once a patient is enrolled or randomized, the study investigators will make every reasonable effort to follow the patient for the entire study period. This trial does not entail a long follow-up period, thus the rate of loss-to-follow-up is anticipated to be negligible.

### Data management {19}

Data entry will be carried out by the investigators of each study center after the participation in training session before the beginning of the study to standardize procedures, including data collection.

Investigators may contact the coordinating center to solve issues that may arise.

Only authorized staff will be able to access the REDCap system. A two-step login procedure is needed to access the system. The first step requires the login with username and password. After the completion of the first step, an e-mail is sent to the user by the system with a verification code to be entered in the second step login, which expires after two minutes.

Investigators will only be granted access to the records of their own patients but not to those stored in the entire database.

The data will be automatically stored by REDCap, with backups planned every 4 h.

During the creation of data collection sheets, when possible, the data format and range of plausible values will be set. If the input value is outside the defined range, a warning message will automatically appear to the researcher.

Data will first be collected with a paper support and, after having checked for completeness and consistency, will be entered in REDCap.

After the end of data collection:

Data provided by the centers will be checked for missing data, plausible, possible, or non-permitted value ranges. When necessary, centers will be asked to correct them;Statistical techniques to identify inconsistencies will be applied periodically. The centers will be notified about eventual inconsistencies to correct them;The coordinating center will review detailed reports on screening, inclusion, follow-up, and data consistency and completeness. The coordinating center will take immediate action to solve any problems that may arise.Data will be entered in the final electronic database only after the CRFs have been cleared by the coordinating center.

### Confidentiality {27}

The electronic CRF, which will not include any names, initials, dates of birth, or local hospital patient numbers, is identified by a unique subject identifier. Data protection in the database will be guaranteed through encoding and the use of a secured database with restricted access by individual login and gradated user rights. Lastly, only encrypted data will be centrally stored.

### Plans for collection, laboratory evaluation, and storage of biological specimens for genetic or molecular analysis in this trial/future use {33}

No biological specimens will be collected.

## Statistical methods

### Statistical methods for primary and secondary outcomes {20a}

The analysis will be performed according to the intention-to-treat (ITT) principle. Descriptive statistics will be calculated to summarize patient characteristics collected at study entry according to the randomization group. Categorical variables will be reported as absolute frequencies and percentages. Continuous variables will be represented as mean and standard deviation or median first and third quartiles if not normally distributed according to the Shapiro–Wilk test.

The raw risk of pressure sore will be calculated at each time point as the ratio between the number of subjects who developed a pressure sore at a given time point divided by the number of subjects undergoing NIV at that time point. Patients having a planned break at the time point considered, but not weaned off NIV, will be considered as patients undergoing NIV.

Mixed effect logistic regression models will be used to estimate the risk of pressure sores and the difference between interfaces, including a random intercept to account for clustering of the subjects within the center and repeated measures within patients. The response variable will be the presence/absence of pressure sores, whereas the independent variables will be the treatment, time (12, 24, 36, 48, 60, 72, 84, 96 h), and their interaction. The marginal predicted probabilities estimated by the model will provide the incidence of pressure sores at different times as well as overall. The inclusion of time as a covariate will allow to test the presence of a time trend in the incidence of pressure sores and to investigate the variation of time trends according to treatment group.

If the descriptive statistics will detect unbalanced characteristics between randomization groups (e.g., indication for NIV), the corresponding variables will be added as covariates in the logistic regression model.

Regarding the number of pressure sores, different mixed effect Poisson regression models will be applied: one for each time point to estimate the average number of pressure sores at each time point and a model in which only the highest number of pressure sores will be considered for each patient. Time will be included as offset to evaluate the average number of pressure sores per day.

The grade and location of pressure sores will be summarized using descriptive statistics at each time point.

The analyses will be also performed according to the modified intention-to-treat approach (mITT) excluding subjects with a NIV duration shorter than 12 h to ensure patients in the rotational group performed at least one rotation of the interface.

Regarding the economic evaluation, the incremental cost-effectiveness ratio (ICER) will be calculated considering two outcomes: (i) the proportion of pressure sores and (ii) the patient comfort. ICER, which is the ratio between the difference of each outcome in the two groups (i.e., difference in the proportion of pressure sores or comfort score) and the difference in the average cost for each treatment will allow to evaluate the incremental costs needed to reduce of 1 point the outcomes thanks to interface rotation. The confidence intervals of the ICER will be calculated using the non-parametric bootstrap method. Specifically, the 2.5^th^ and 9.75^th^ percentiles of the bootstrap distribution of ICER will be considered as the lower and higher limits of the confidence interval. The cost-effectiveness acceptability curve will also be drawn to evaluate the probability of the intervention to be cost-effective, considering different thresholds.

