## Introduction

### Background and rationale {6a}

In recent years, noninvasive ventilation (NIV) has increasingly become a common approach for the treatment of hypercapnic [1, 2] and hypoxemic [3] patients both inside [3] and outside [4–6] the intensive care unit (ICU). NIV refers to the delivery of a positive pressure to the patient through interfaces like masks or helmets without the need for invasive endotracheal intubation [7]. These interfaces can efficiently and non-invasively support patients with acute respiratory failure (ARF), preserving airway defense mechanisms, speech, and swallowing, averting the need for prolonged sedation, lowering the occurrence of ventilator-associated pneumonia [8], and ultimately reducing ICU admission [9] and mortality [2]. Nonetheless, NIV failure is observed in 8% of hypercapnic [10] and 50% of hypoxemic patients [11], leading to delayed initiation of invasive ventilation treatment and poor outcomes [5, 10, 12, 13].

As patient comfort is a major factor for NIV success [14], the selection of the most suitable interface type is of paramount importance [15]. Another key variable that should be taken into account to achieve patient comfort and avoid the generation of skin breakdown until pressure ulcers, a frequently observed NIV side effect [7], is the time of exposure to a given interface. Indeed, when the pressure applied between the interface and the skin exceeds the capillary pressure, skin breakdown may occur, resulting in NIV discontinuation due to pain and intolerance [16]. Published incidence rates of facial pressure ulcers associated with NIV masks range from 2 to 31% [17–22] depending on the type of mask used, length of treatment, ventilator setting, humidification, nutritional status, and preventative measures adopted.

The development of pressure ulcers is associated with adverse outcomes that may contribute to patient pain and suffering, impaired quality of life [23], and increased hospital costs [24, 25].

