Stage II	The skin blisters or forms an open sore. The area around the sore may be red and irritated.
Stage III	The skin now develops an open, sunken hole called a crater. The tissue below the skin is damaged. It is possible to see body fat in the crater.
Stage IV	The pressure ulcer has become so deep that there is damage to the muscle and bone, and sometimes to tendons and joints.
Unstageable	Is not possible to see the bottom of the sore, and it is impossible to establish how deep it is
Suspected deep tissue injury	The surface of the skin looks like a Stage 1 or 2 sore, but underneath the surface, it appears as a Stage III or IV.

Discomfort due to the mask will be evaluated every 12 h using a 5-level Likert-like scale [17, 37] to answer the questions “How is your level of discomfort related to the mask?”. The extremes of the scale are “1—no discomfort” and “5—unbearable discomfort,” with three intermediate levels: “light discomfort,” “moderate discomfort,” and “intense discomfort”).

In both groups, in case of the presence of a new pressure ulcer, the strategy that can be applied comprehend (1) application of a wound care dressing or a different kind of wound care dressing; (2) reduction of the time spent on NIV; and (3) change interface.

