### Outcomes {12}

The primary effectiveness outcome is the proportion of patients developing at least one pressure sore of any stage at 36 h from randomization. The reason why this measure of effectiveness was chosen is that it is more clinically relevant than the overall number of pressure sores. Furthermore, 36 h seems to be an appropriate time point given that the time it takes for pressure sores to develop is extremely variable, but it might as well be very short.

Secondary outcomes will be the onset, number, and stage of pressure sores and comfort during NIV measured at different time points (12, 24, 36, 48, 60, 72, 84, 96 h). At the same time points, the location of pressure sores per patient will also be recorded, i.e., forehead, nose bridge, left cheek, right cheek, chin, left periauricular, right periauricular, and occipital. The study will also monitor the number of patients that interrupts NIV due to discomfort, the presence/absence of eye irritation in relation to both oronasal and full face/hybrid mask, poor adherence to the protocol (e.g., duration of NIV treatment/day, interfaces changed and hygiene protocol application both during each 12-h protocol period) and the presence/absence and types of vasoactive medications, i.e., epinephrine, norepinephrine, vasopressin, dobutamine, dopamine, other. Further outcomes include the costs for intervention implementation (e.g., mask-related costs) and those related to the care of pressure sores (antibiotic treatment, specialist medical visits).

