### Participant timeline {13}

Patients will be screened for eligibility criteria. Consent will be obtained from the patients, if possible, or their legal representative. Thereafter, patients will be randomized into the treatment or control group. After randomization, the skin underneath the mask and the auricle and occipital regions will be inspected to check for any possible pressure sores every 12 h for the following 4 days. Patient status at hospital discharge will also be evaluated (Fig. 2).

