### Methods in analysis to handle protocol non-adherence and any statistical methods to handle missing data {20c}

Protocol non-adherence will be handled by performing the analyses according to the ITT principle, specifically, patients will be analyzed considering their allocation group regardless of the intervention they will follow. Moreover, deviation from the protocol will be registered as well as the reason for deviation. The missing rate is expected to be very low, therefore no specific analyses to handle missing data are planned. However, if needed (i.e., missing rate between 20 and 40%) multiple imputation through expectation–maximization algorithm will be applied and the results obtained from analysis of the new data will be considered as sensitivity analysis.

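### The raw 36 h risk counts only patients still on NIV in its denominator, which contradicts the primary outcome and the ITT principle

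*Protocol article*

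**What the plan says.** Outcomes {12} defines the primary outcome as "the proportion of patients developing at least one pressure sore of any stage at 36 h from randomization". Nothing there requires the patient to be on NIV at 36 h.

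Statistical methods {20a} opens with the ITT principle, and section {20c} spells it out: "patients will be analyzed considering their allocation group regardless of the intervention they will follow".

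Section {20a} then defines the raw risk at each time point as the number of subjects who developed a sore at that point "divided by the number of subjects undergoing NIV at that time point". The next sentence counts patients on a planned break as on NIV provided they are not weaned. Weaned patients are therefore left out on purpose.

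The paragraph after that assigns the estimate of risk and the difference between strategies to mixed effect logistic models with treatment, time and their interaction. Their marginal predicted probabilities are to give the incidence at each time. It does not state which patients or visits enter these models.

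Participant timeline {13} says that after randomisation "the skin underneath the mask and the auricle and occipital regions will be inspected" every 12 h for four days.

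**The concern.** Being on NIV at 36 h is decided after randomisation. Criteria for discontinuing {11b} names improvement, intubation and death as reasons to stop. Background {6a} adds that skin breakdown can end NIV through pain and intolerance, and Outcomes {12} tracks patients who interrupt NIV because of discomfort. The denominator can therefore depend on the outcome itself. Participants and carers are unblinded ({17a}), so it can also depend on arm. A ratio built this way no longer compares the groups as randomised.

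The numerator is unclear too. If it is limited to patients on NIV, a sore recorded at 24 h in a patient weaned by 36 h disappears. If it is not, numerator and denominator cover different people.

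At stake are the reported primary proportion, possibly the treatment comparison, and the interim stopping test, which section {21b} words as a test of the sore incidence rate.

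**Working it through.** **1. The plan's own sample size.** Inputs from Sample size {14}: 23% in controls, a 10-point absolute difference (taken as 23% vs 13%), type I error 0.05 (two-sided assumed), power 0.80, dropout 5%, stated n = 239 per group.

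- Unpooled variance: (1.960 + 0.842)² × (0.23×0.77 + 0.13×0.87) / 0.10² = 228, and 228/0.95 = 240.
- Pooled variance: 231, and 231/0.95 = 244.

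Both agree with 239 to within 3%. After 5% dropout, 239 × 0.95 = 227 per arm are evaluable.

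Power = Φ{[d − 1.96·√(2p̄(1−p̄)/n)] / √[(p₁(1−p₁) + p₂(1−p₂))/n]}. With n = 227, d = 0.10 and p̄ = 0.18 this is Φ[(0.100 − 0.0707)/0.0357] = 79%.

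**2. The on-NIV risk.** Let p be the true risk of a sore by 36 h, u the share off NIV at 36 h among patients without a sore, and v the share among those with one.

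- On-NIV share: s = p(1−v) + (1−p)(1−u).
- Reading A, numerator limited to patients on NIV: p(1−v)/s.
- Reading B, numerator with all sores: p/s.

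The documents give neither u nor v. All values below are assumptions.

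**3. Stopping unrelated to sores (u = v), true risks 23% vs 13%, Reading A.** The risks do not change, but the number does.

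| Off NIV at 36 h | Evaluable per arm | Power |
|---|---|---|
| 0% | 227 | 79% |
| 10% | 204 | 75% |
| 20% | 182 | 70% |
| 30% | 159 | 64% |

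**4. No true effect (18% in both arms), stopping after a sore differs by arm, Reading A.**

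- Mild: u = 5%; v = 15% in one arm and 5% in the other. First arm: s = 0.153 + 0.779 = 0.932, risk 0.153/0.932 = 16.4%. Second arm: 0.171/0.950 = 18.0%. Spurious difference 1.6 points; two-sided rejection about 7%.
- Strong: u = 20%; v = 40% and 20%. First arm: s = 0.108 + 0.656 = 0.764, risk 0.108/0.764 = 14.1%. Second arm: 18.0%. Spurious difference 3.9 points; rejection about 17%.

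The nominal rate is 5%. The direction depends on which arm stops more often after a sore.

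**5. The numerator.** Take true risks 23% vs 13%, u = 20%, v = 50%, so s = 0.731 and 0.761.

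- Reading A: 0.115/0.731 = 15.7% vs 0.065/0.761 = 8.5%.
- Reading B: 0.23/0.731 = 31.5% vs 0.13/0.761 = 17.1%.

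The same data thus give two quite different results, and neither is the 23% vs 13% that the primary outcome describes.

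**The case against.** The strongest reply is that the rule is written for the raw risk, while the treatment comparison belongs to the mixed model, where no on-NIV restriction appears. That stands. A reader might infer that the planned comparison is itself confined to patients on NIV, but the document does not say so. The model also uses the 12 h and 24 h records, so a sore seen at 24 h in a patient later weaned can still inform it. Steps 3 and 4 use a two-proportion test that the plan does not name, and say nothing about the size of any bias in the model.

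Three other inferences are not supported:

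- *That cutting back NIV after a sore removes the patient.* Section {11a} does list "reduction of the time spent on NIV" as a response, but a patient on a planned break and not weaned stays in the denominator. Only those off NIV at the time point are lost.
- *That many patients must be off NIV by 36 h.* Background {6a} says "NIV failure is observed in 8% of hypercapnic" patients, but with no time frame. For NIV given to avoid or replace invasive ventilation, section {11d} describes a typical course of two to three days. The larger assumed shares may be too high, hence the mild scenario.
- *That the mITT set is flawed in the same way and for a wrong reason.* It is an additional analysis, and with a change every 6 h, 12 h of NIV is enough "to ensure patients in the rotational group performed at least one rotation of the interface".

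Finally, section {13} sets no on-NIV condition for the skin checks, but it does not expressly say that they continue once NIV has ended.

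None of this removes the contradiction. The denominator is a stated rule rather than a detail left open, and it applies at the primary time point.

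**Conclusion.** The raw-risk definition is wrong as written. At 36 h it does not estimate the primary outcome in {12}, does not follow ITT as stated in {20a} and {20c}, and conditions on a state that the outcome can influence. Its numerator can be read in two ways, and each is unsatisfactory. Whether the treatment comparison inherits the bias cannot be settled from the document, because the mixed model's analysis set is not stated: it does so only if the model uses the same restriction.

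The size is illustrative. For a simple comparison of raw 36 h risks, power would fall from 79% to between 75% and 64% with 10% to 30% off NIV. Under no effect, rejection would be about 7% in the mild scenario and about 17% in the strong one. These figures rest on assumed off-NIV shares and on Reading A of the numerator.

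**What to change.** For the primary analysis and the interim test:

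- Denominator: all randomised patients, by allocated arm.
- Event: any new sore recorded at any inspection from randomisation up to and including 36 h, whatever the NIV status at 36 h. A sore recorded earlier remains an event.
- Patients weaned, intubated or dead before 36 h stay in the denominator with their observed sore status. Add a competing-event cumulative incidence as a sensitivity analysis.
- State that the mixed model uses this same set.
- State that the scheduled 12-hourly skin checks continue after NIV stops.
- Report the on-NIV risk as descriptive only.

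The cost is wording in the protocol and analysis plan. The inspections are already scheduled every 12 h for four days, and the stated 239 per group need not change: about 227 evaluable per arm still gives 79% power at 23% vs 13%. The small downside is that the control risk among all randomised patients may lie a little below 23%, and the power statement should say so.
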